### Outcomes {12}

#### Primary outcome measures

The primary outcome is transcultural competence. Transcultural competence will be assessed at the beginning of the training, at the end of the training, and at the 2- and 6-month follow-up (see Fig. 1). For this purpose, the well-validated Multicultural Counseling Inventory (MCI) [44], translated into German by [name] [22], is used. The MCI captures general transcultural competence as conceptualized by Sue et al. [34]. With a total of 40 items, transcultural competence is assessed on the subscales *skills* (11 items, e.g., “I am able to quickly recognize and recover from cultural mistakes or misunderstandings.”), *cultural self-awareness and other-awareness* (10 items, e.g., “In order to be able to work with minority clients, I frequently seek consultation with multicultural experts and attend multicultural workshops or training sessions.”), and knowledge (11 items, e.g., “I use innovative concepts and treatment methods.”). In an additional fourth subscale, *therapeutic relationship* is assessed (8 items, e.g., “I am confident that my conceptualizations of client problems do not consist of stereotypes and biases.”). The MCI allows to compute both a total score and scores for the four subcategories. The 40 self-report items are answered on a 4-point Likert scale ranging from 1 (very inaccurate) to 4 (very accurate). Research indicates that the MCI is a suitable psychometrically robust instrument for evaluating transcultural competence in multicultural training processes [61]. The dimensions appeared to be distinct yet interrelated [61]. Internal consistency reliabilities (Cronbach’s alpha) ranged from .67 to .81 in the subscales and .86 for the full scale [44].

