**Fig. 1 Fig1:**
[figure not shown]
Schedule of enrolment, interventions, and assessments

A second questionnaire on transcultural competencies is included, which was specifically developed for the German psychotherapeutic setting, the OnTracc-questionnaire [45]. It contains 28-self-report statements, which are based on three factors, *engagement* (7 items, e.g., “I am actively involved in the process of reducing barriers for refugees and people with a migration background in accessing psychotherapy (e.g. against the shortage of translators).”), *awareness* (10 items, e.g., “I take cultural related differences in symptom description into account.”), and *challenges* (11 items, e.g., “I worry about my skills to work with refugees, because they have a different understanding of diseases and mind.”). The items are rated on a 5-point Likert scale from 1 (totally disagree) to 5 (totally agree). The OnTracc-questionnaire showed substantial convergent and discriminant validity to the MCI subscales and good reliability for all subscales (McDonald’s omega between .73 and .81) [45]. The OnTracc-questionnaire was likewise recommended for evaluating transcultural competence in training [45].

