#### Secondary outcome measures

In addition to transcultural competence, secondary outcomes serve to explore concrete experiences in treating patients with diverse cultural backgrounds. Eight items are used for this purpose. For example, the number of patients with diverse cultural backgrounds who are currently being treated by each participant in their clinical practice is recorded. The participants are further asked whether they are supervised in the field of transcultural therapy and whether they have ever worked with a language mediator. A 6-point Likert scale will additionally be used to assess satisfaction in therapies with patients with diverse cultural backgrounds and perceived competence. The items were taken from a preliminary study [62].

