## Statistical methods

### Statistical methods for primary and secondary outcomes {20a}

Outcomes will be evaluated using intention-to-treat (ITT) analysis. Group differences (group: training group vs. waitlist control group) in primary (transcultural competence; MCI and OnTracc) and secondary outcomes (experiences in treating people from other cultures) will be examined using piecewise linear mixed-effects models with repeated measures (time point: pre, post, follow-up 1). Likely will piecewise linear mixed-effects models be used to examine the longer-term effect of the training (including the four time points: pre, post, follow-up 1, and follow-up 2). The significance level will be set at *p* < .05.

Sociodemographic data will be listed by group condition and for the total group. Group comparisons will be examined at baseline to check for successful randomization. Categorical data are reported as *N* (%), continuous data as mean (SD).

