### Methods for additional analyses (e.g., subgroup analyses) {20b}

Regarding additional analyses, we would like to examine the clinical psychologist’s socio-demographic influence on the outcomes (e.g., age, duration of activity as a therapist, own migration background, multilingualism, volunteering for refugees and patients from different countries). We will investigate socio-demographic variables and disparities, including an examination of potential differences in the dependent variable among the three German-speaking countries. Furthermore, a consistency test will be performed to compare the post-intervention effects between the training group and the waitlist control group. For this purpose, two models are computed, one with the group as a predictor and one without, and the two models are compared with each other. We also would like to examine the influence of adherence on the outcomes by means of completed modules by a logistic regression.

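### The adherence analysis names a logistic regression, which does not fit the primary MCI and OnTracc scores; of the outcomes described, only two yes/no secondary items suit it directly

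*Protocol article*

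**What the plan says.** The section on additional analyses {20b} contains the plan's only sentence on analysing adherence: "We also would like to examine the influence of adherence on the outcomes by means of completed modules by a logistic regression". It does not say which outcomes are meant and describes no yes/no version of any of them.

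The primary outcomes are two questionnaires. For the first, under Primary outcome measures, "The MCI allows to compute both a total score and scores for the four subcategories". The second, the OnTracc questionnaire, has 28 statements in three factors, and "The items are rated on a 5-point Likert scale from 1 (totally disagree) to 5 (totally agree").

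The secondary outcomes are of mixed type. For one, "the number of patients with diverse cultural backgrounds who are currently being treated by each participant in their clinical practice is recorded". Participants are also asked "whether they are supervised in the field of transcultural therapy and whether they have ever worked with a language mediator". Finally, "A 6-point Likert scale will additionally be used to assess satisfaction in therapies with patients with diverse cultural backgrounds and perceived competence".

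The main analysis in {20a} covers both primary and secondary outcomes and uses "piecewise linear mixed-effects models with repeated measures (time point: pre, post, follow-up 1").

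**The concern.** A binary logistic regression needs a dependent variable with two values. The MCI and OnTracc scores have many, and the article gives no cut-off or responder definition for either. For these scores, {20b} therefore names a model that cannot be fitted as it stands and that belongs to a different family from the one {20a} uses for the same variables.

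If the sentence were followed literally, someone would have to split the scores first. A split discards information, and the result depends on where the cut is placed. The answer would also come out as an odds ratio, which cannot be set beside a training effect in score units.

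**Working it through.** **1. Figures available.** The plan gives no figure for the adherence analysis. Its sample size (N = 174, 1:1) concerns the group-by-time model, and the point does not depend on it. It is used here only for the size of one arm: 174 / 2 = 87.

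**2. Scale of each outcome against the named model.** Item counts and response ranges come from the outcome sections. I assume summed scores; averaging leaves the number of possible values the same.

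| Outcome | Possible values | Binary logistic model without a cut? |
|---|---|---|
| MCI total, 40 items scored 1-4 | 40 to 160, so 160 - 40 + 1 = 121 | No |
| Shortest MCI subscale, 8 items | 8 to 32, so 25 | No |
| OnTracc, 28 items scored 1-5, if totalled | 28 to 140, so 113 | No |
| Shortest OnTracc factor, 7 items | 7 to 35, so 29 | No |
| Number of patients treated | Count | No |
| Satisfaction; perceived competence | 6 ordered categories | No; an ordinal logistic model could take them, but none is named |
| Transcultural supervision; ever worked with a language mediator | Yes/no by wording | Yes |

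The article mentions eight secondary items and describes only some of them, so the table covers those described.

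**3. Could the roles be reversed?** With completion of all six modules as the dependent variable, logistic regression would fit. It would then ask what predicts adherence. The sentence asks about the influence of adherence on the outcomes, which is the opposite direction.

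**4. What a split would cost (illustration only).** For a normal score and a weak association, a median split keeps about 2/π = 0.637 of the information: 87 × 0.637 = 55 effective participants, or 174 × 0.637 = 111.

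Two simulations compared linear regression on the score with logistic regression on the split score (likelihood-ratio test, α = 0.05). Assumptions not in the article: module-score correlation as shown, 65% completing all six modules, and a score for every participant.

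| n | Correlation | Cut | Linear | Logistic | Runs |
|---|---|---|---|---|---|
| 87 | 0 | median | 0.048 | 0.046 | 2000 |
| 87 | 0.2 | median | 0.469 | 0.337 | 2000 |
| 87 | 0.3 | median | 0.837 | 0.626 | 2000 |
| 87 | 0.3 | median | 0.837 | 0.670 | 1000 |
| 87 | 0.3 | 70th percentile | 0.804 | 0.551 | 1000 |
| 87 | 0.3 | 85th percentile | 0.834 | 0.372 | 1000 |
| 174 | 0.3 | median | 0.983 | 0.910 | 1000 |
| 174 | 0.3 | 70th percentile | 0.992 | 0.844 | 1000 |
| 174 | 0.3 | 85th percentile | 0.987 | 0.667 | 1000 |

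The linear model does not use the cut, so the variation in its column at a given n and correlation is simulation noise. At correlation 0.3 with a median split, the loss is 0.837 - 0.626 = 0.21 or 0.837 - 0.670 = 0.17 at n = 87, and 0.983 - 0.910 = 0.07 at n = 174. Set against the other linear value, 0.992, it is 0.08.

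**The case against.** A reader might infer that the adherence analysis as a whole can be run only after cutting continuous scores. The article does not support that. The sentence in {20b} refers to the outcomes without restriction, and the secondary outcomes include two yes/no items that need no cut.

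Nor does {20a} sort outcomes by scale. It assigns linear mixed models to every primary and secondary outcome, including the yes/no items and the patient count. It shows that the plan treats the MCI and OnTracc scores linearly, but it is not a considered statement about each outcome.

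A reader might also infer that a cut-off will be picked after the data are seen. The article does not say so. A responder definition for an additional analysis could sit in a statistical analysis plan that is not shown, and its absence here is not a fault in itself.

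The larger power loss, about 21 points, counts the training group only. Under Participant timeline {13} the waitlist group is trained and assessed too, so up to 174 people could have module counts, and the median-split loss is then about 7 to 8 points. Complete scores are doubtful as well: under {11c}, participants who stay inactive and do not reply are treated as dropouts.

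All of this stands, and it narrows the point without removing it. The protocol did not leave the model open. It named one, and that model does not match the scale of the primary outcomes. An analysis plan that followed the sentence would inherit the mismatch.

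**Conclusion.** The point holds for the primary outcomes. Logistic regression does not fit the MCI and OnTracc scores, which {20a} models linearly and for which no dichotomy is defined. Among the secondary outcomes described, only the supervision and language-mediator items suit it directly.

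Severity is minor. The analysis is listed as additional, is worded as a wish, and adherence is not among the stated objectives {7}. The primary analysis, the sample size and the efficacy conclusion are untouched. The power figures show only what a split could cost under assumed inputs; they do not predict a loss in this trial. The point concerns the choice of model, not how an association between modules and outcomes should be interpreted.

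**What to change.** In {20b}, replace the logistic regression with a linear (mixed) model of the MCI and OnTracc scores on the number of completed modules, adjusted for the t0 score and reported in score units. Name the dependent variables. Keep logistic regression only for the yes/no secondary items, or for a separately named analysis of what predicts completing all six modules. State whether the analysis uses the training group alone or also the waitlist group after its own training.

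The cost is a sentence or two in the analysis section. No new data, assessments or participants are needed.

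### The adherence analysis names logistic regression for outcomes that include the MCI and OnTracc scores, which are not binary and which the main analysis treats as continuous

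*Protocol article*

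**What the plan says.** The adherence analysis is the last item in the section on additional analyses {20b}. The team wishes to "examine the influence of adherence on the outcomes by means of completed modules by a logistic regression". The sentence does not say which outcomes are meant, and it gives no cut-off or responder definition.

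The outcomes are described under Outcomes {12}:

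- **MCI (primary).** "The 40 self-report items are answered on a 4-point Likert scale", and "The MCI allows to compute both a total score and scores for the four subcategories".
- **OnTracc-questionnaire (primary).** It has 28 statements rated from 1 to 5, grouped into three factors of 7, 10 and 11 items.
- **Secondary items.** These include a count of patients currently treated, 6-point ratings of satisfaction and perceived competence, and two questions that appear to be yes/no: "whether they are supervised in the field of transcultural therapy and whether they have ever worked with a language mediator".

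For the main analysis, section {20a} says that group differences in the primary and secondary outcomes "will be examined using piecewise linear mixed-effects models with repeated measures".

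**The concern.** Two sections of the same article name models for the primary outcomes that assume different kinds of dependent variable. A linear mixed model takes a score as it is. A binary logistic regression needs a variable with two values. As section {20b} is worded, an analyst would have to cut the MCI and OnTracc scores in two, drop them from the adherence analysis, or depart from the stated method. Cutting them discards information, and the result then depends on where the cut is placed. What is at stake is how precise and how interpretable the adherence result is. The efficacy result is not involved.

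**Working it through.** The plan gives no figure for this analysis, so there is none to reproduce. The check compares the model with the type of outcome, and then works out what dichotomising would cost.

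**Step 1: direction of the regression.** Section {20b} speaks of the influence of adherence on the outcomes and measures adherence by completed modules (0 to 6, since the training has six). Modules are the predictor and outcomes are the response. If completion (yes/no) were the response, logistic regression would fit, but the sentence has the opposite direction.

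**Step 2: type of each response.** A scale of k items, each with m categories, can take k × (m − 1) + 1 distinct values, whether it is summed or averaged.

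| Outcome | Items × categories | Possible values | Binary? |
|---|---|---|---|
| MCI total | 40 × 4 | 40 × 3 + 1 = 121 | No |
| MCI subscales | 8 to 11 × 4 | 8 × 3 + 1 = 25, up to 11 × 3 + 1 = 34 | No |
| OnTracc factors | 7 to 11 × 5 | 7 × 4 + 1 = 29, up to 11 × 4 + 1 = 45 | No |
| Patients treated | count | many | No |
| Satisfaction, perceived competence | 6-point ratings | 6 | No |
| Supervision, language mediator | yes/no (apparently) | 2 | Yes |

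**Step 3: can the model be fitted directly?** A binary logit was tried on a simulated score on the 1 to 4 scale. The software rejected it because the response must lie between 0 and 1. The score has to be split first.

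**Step 4: cost of a split.** Assume a normally distributed score cut at its q-th quantile, c. For a weak association, the information kept relative to a linear model is

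efficiency = φ(c)² / [q(1 − q)],

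where φ is the standard normal density. At the median, c = 0 and φ(0)² = 1/(2π), so efficiency = [1/(2π)] / 0.25 = 2/π = 0.637.

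| Cut at | Information kept |
|---|---|
| 50th percentile | 64% |
| 70th percentile | 58% |
| 80th percentile | 49% |
| 90th percentile | 34% |

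The median is the best case, so at least about 36% is lost. The plan names no cut. These figures show the range of what a split would cost and do not describe a planned procedure.

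**The case against.** The strongest reply is that the sentence refers to the outcomes in general and never names the primary scores. Logistic regression is right for the two items that appear to be yes/no, and an ordinal logistic model could serve the 6-point ratings with little loss. A cut-off for an exploratory analysis may also properly be left to an analysis plan that is not shown. Much of this stands. The mismatch does not extend to every outcome, and the absence of a cut-off is not in itself a fault. What remains is that the article does not leave the model open. It names one, does not restrict it to the yes/no items and does not call it ordinal, while section {20a} models the same primary scores linearly.

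A reader might infer several stronger points that the documents do not support:

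- **That low adherers will be missing because their participation is deleted.** Section {11c} says that participation is deleted after prolonged silence. It does not say that collected data are erased, and section {20c} enters all randomised participants in the analyses.
- **That the loss can be stated as a number of training-group members.** No median split is planned. The waitlist group also takes the training and is assessed afterwards (section {13}), so module counts will exist for both arms.
- **That a data-driven split is intended.** Nothing in the article says so.
- **That a complier-average analysis is needed.** This would be a further estimand, with a completion threshold that the article does not contain. It would also assume that completing fewer modules has no effect.

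Self-selection is a genuine limit: motivated participants may both complete more modules and rate themselves higher. It applies equally to a linear model, so it bears on how the result is described and does not count against logistic regression as such.

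**Conclusion.** The method is wrong as written for the MCI and OnTracc scores. The named binary model does not match them, conflicts with the linear models in section {20a}, and has no defined binary endpoint to work on. If the scores were dichotomised, at most about 64% of the information would remain, assuming a normal score, a weak association and the most favourable cut. The model also does not suit the patient count or, in its binary form, the 6-point ratings. It is appropriate for the two secondary items that appear to be yes/no.

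The point is minor. The analysis is exploratory and stated as a wish. The primary comparison, the sample size of 174 and the intention-to-treat principle do not depend on it.

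**What to change.** Amend the sentence in section {20b} as follows:

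- For MCI and OnTracc, use a linear or linear mixed model of the post-training score on the number of modules completed, adjusted for the baseline score and prior transcultural training.
- Report the result as an association, not as an effect of adherence.
- Keep logistic regression for the supervision and language-mediator items only. If the count and the ratings are to be included, name a model that suits each.
- State whether the analysis covers the training group alone or both arms once the waitlist group has been trained.

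The cost is a short text change and a few lines of code. The scores are collected at every assessment, and prior training is among the baseline control variables, so no new data are needed.

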### Methods in analysis to handle protocol non-adherence and any statistical methods to handle missing data {20c}

The data are analyzed according to the intention-to-treat principles, and data of all individuals randomized in this trial will be entered in our analyses. The handling of missing data is reported in tables and results.

### Plans to give access to the full protocol, participant-level data, and statistical code {31c}

The complete protocol of the presented study is in this document. On request, participant-level data, statistical code, or documentation can be provided by the authors.

## Oversight and monitoring

### Composition of the coordinating center and trial steering committee {5d}

The trial team consists of six researchers who exchange information on the progress of the study at two-week intervals. The principal investigator holds ultimate oversight of the study. The study coordinator is responsible for data collection and mentoring the supervisors. The supervisors are in charge of supervising the participants, i.e., they give feedback on the modules completed. The supervisors and the study coordinator will meet on a weekly basis to discuss upcoming issues concerning the supervision of participants. Due to the small project team, a Trial Steering Committee will not be constituted.

### Composition of the data monitoring committee, its role, and reporting structure {21a}

n/a. No extra monitoring committee is formed due to the fact the trial does not include a clinical sample and is a monocentric trial. The data monitoring is conducted by one of the investigators who is not directly involved in data collection.

### Adverse event reporting and harms {22}

n/a. Adverse event reporting and harms are not explicitly surveyed as the study does not include a clinical sample. Participants are informed that they can contact the study team, the study coordinator, or the principal investigators for questions or uncertainties.

### Frequency and plans for auditing trial conduct {23}

n/a. We will not install a Data Monitoring Committee for this trial, given that this is not a clinical trial involving a clinical sample, but an educational, low-risk intervention for clinical psychologists. The trial will be monitored by the principal investigator and three members of the research team. The supervisors and the study coordinator will meet on a weekly basis to discuss upcoming issues.

### Plans for communicating important protocol amendments to relevant parties (e.g., trial participants, ethical committees) {25}

Important protocol modifications (e.g., changes to eligibility criteria, outcomes) will be communicated to and must be approved by the local Ethics Committee. In addition, the protocol would be updated and the trial registry would be adjusted.

